### Sample size calculations

Referring to the distribution of the mRS at the 90 days after stroke onset in the Chinese National Stroke Registry Study, it was found that the proportion of mRS ≤ 2 was 64.6%. In the control group, the percentage of participants with mRS ≤ 2 was 65%, while in the intervention group, the proportion would be 76.5%.The sample size was calculated using PASS 21.0.2.The difference test between the two sample rates was used to calculate the sample size, and a 1:1 design was conducted at the testing level α=0.05 (bilateral) and 1-βß0.8. Considering a 20% dropout rate, each group should include 240 cases, bringing the total number of cases to 480.

$$n = {{2pq{{\left( {z{{\kern 1pt} _\alpha } + {z_\beta }} \right)}^2}} \over {{{\left( {p1 - p2} \right)}^2}}}$$

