## Methods

### Study design

The FAST trial is a prospective, multicenter, randomized, double-blind, placebo-controlled study. This study will enroll 480 subjects. Eligible patients will be assigned to the YQFM group or placebo injection group at a 1:1 ratio and stratified blocked randomization by the study center.The main purpose of the experiment is to test if YQFM is more effective than a placebo in achieving a favorable functional status, defined as an mRS score ≤ 2 at 90 days in patients with AIS. Figure 1 shows the flow diagram of this experiment. The study protocol was described, and a complete checklist is available according to the Standard Protocol Items: Recommendations for Interventional Trials (SPIRIT) guidelines (see Additional File 2 in Supplementary Material) [29].

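### 480 patients do not give the stated 80% power at two-sided 5%: after the plan's own 20% dropout, power is about 70%

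*Protocol article*

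**What the plan says.** All the inputs are in the protocol article under "Sample size calculations".

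- Control rate: "In the control group, the percentage of participants with mRS ≤ 2 was 65"%, rounded from a national registry in which "it was found that the proportion of mRS ≤ 2 was 64.6"%.
- Treated rate: "while in the intervention group, the proportion would be 76.5"%.
- Error rates: "a 1:1 design was conducted at the testing level α=0.05 (bilateral) and 1-βß0.8". The sign before 0.8 is garbled in the text; I read it as power of 0.8.
- Result: "Considering a 20% dropout rate, each group should include 240 cases, bringing the total number of cases to 480".

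The section states that the size came from a two-proportion comparison in PASS. It then prints a formula in which 2pq times the squared sum of z-alpha and z-beta is divided by the squared difference in rates. The subscript is alpha, not alpha/2, and is not defined. Allocation is 1:1 ("Study design"). The primary test is a chi-squared test, with a missing primary outcome carried forward ("Data analysis"). No one-sided test is stated anywhere.

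**The concern.** The section declares a two-sided test and says that 240 per group already allows for 20% dropout. A quick check puts the two-sided requirement near 245 evaluable per arm before any allowance for dropout, so both statements cannot be true of 240.

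This section is the only justification for the trial's size. If its power is overstated, a non-significant result will be taken as stronger evidence against a benefit than it is. The interim look at 50% turns on whether efficacy can still be shown at the end, so it would also start from the wrong power.

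**Working it through.** **Inputs.** p1 = 0.65, p2 = 0.765, difference d = 0.115; mean p = 0.7075, q = 0.2925, so 2pq = 0.4139; d² = 0.013225. The sum of the two binomial variances is 0.65×0.35 + 0.765×0.235 = 0.4073. z for 80% power = 0.842. The critical value is 1.960 for two-sided 0.05 and 1.645 for one-sided 0.05. Dropout of 20% is applied as n/0.8.

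**1. Trying to reproduce 240**

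| Form | Two-sided 0.05: evaluable | ÷ 0.8 | One-sided 0.05: evaluable | ÷ 0.8 |
|---|---|---|---|---|
| Printed formula, 2pq(z+z)²/d² | 245.6 | 307.0 | 193.5 | 241.9 |
| Pooled under the null, unpooled under the alternative | 244.5 | 305.6 | 192.4 | 240.5 |
| Unpooled variance | 241.7 | 302.1 | 190.4 | 238.0 |
| Arcsine | 243.5 | 304.4 | 191.8 | 239.7 |

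First row, two-sided: 0.4139 × (1.960 + 0.842)² / 0.013225 = 0.4139 × 7.849 / 0.013225 = 245.6. One-sided: 0.4139 × 6.183 / 0.013225 = 193.5.

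Rounded up, the two-sided requirement is 303 to 308 per arm. Taking 245 evaluable from the second row gives 245/0.8 = 306.25, so 307 per arm and 614 in total. The shortfall is 307 − 240 = 67 per arm, or 134 in total. The continuity-corrected version is larger still: 262 evaluable, 328 per arm. Inflating by ×1.2 instead of ÷0.8 gives at least 290 per arm, so that does not recover 240 either. Once dropout is included, 240 appears only with one-sided 0.05.

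**2. Power of the design as written**

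Power = Φ{[d√n − z_crit·√(2pq)] / √0.4073}, with √(2pq) = 0.6433 and √0.4073 = 0.6382.

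- 192 per arm (240 × 0.8), two-sided: (1.5935 − 1.960×0.6433)/0.6382 = 0.521, power **69.9%**. Exact enumeration of the uncorrected chi-squared test gives 70.1%.
- 192 per arm, one-sided: (1.5935 − 1.645×0.6433)/0.6382 = 0.839, power 79.9%.
- 240 per arm, no loss, two-sided: (1.7816 − 1.960×0.6433)/0.6382 = 0.816, power **79.3%** (exact 79.5%).

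**3. Detectable difference.** With 192 per arm, two-sided power first reaches 80% at 77.9% against 65%, which is 12.9 points. With 240 per arm it does so at 76.6%, which is 11.6 points.

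**4. Using the registry rate.** If the control rate is 64.6% and the treated rate stays at 76.5%, the two-sided requirement is 230 evaluable and 288 randomised per arm (576 in total). Power at 192 per arm is then 72.7%. Rounding of the control rate does not explain the gap.

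**The case against.** **The cause is inferred.** The undefined z-alpha could stand for the two-sided critical value, since the text calls alpha bilateral, and the software run need not have used the printed formula. The two-sided number before dropout (242 to 246) is also within about 2.5% of 240, so the dropout step may simply have been left out. This stands: a one-sided value is the likeliest explanation, not a proven one. It does not rescue the figure, because the section says 240 already allows for dropout, and under either slip 192 evaluable patients per arm give about 70% power.

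**Dropouts may stay in the analysis.** The plan carries forward a missing primary outcome, and the visit chart has an mRS at day 30, so patients lost after that visit would still be counted. With all 240 per arm analysed, power is 79.3% if carried-forward values dilute nothing. If the 11.5-point difference shrinks by 5%, 10% or 20%, it is 74.8%, 69.9% or 59.2%. This partly stands: 70% is the figure when dropouts contribute no outcome, and it is neither a floor nor a ceiling. But no version with the stated inputs reaches 80%, and counting all 240 as evaluable contradicts having inflated for dropout.

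**An article condenses the full protocol.** That excuses omissions. Here the inputs and the result are both printed, and they disagree.

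**Conclusion.** The concern holds. From the stated rates, two-sided 0.05, 80% power and 20% dropout, the requirement is about 307 per arm, not 240. The planned 480 patients give 69.9% power when 20% supply no outcome and 79.3% when all do. The risk of missing the planned effect after dropout is therefore about 30%, where the plan implies 20%.

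These figures assume the plan's own rates, an uncorrected chi-squared test and equal dropout in both arms. They leave out any loss of power from the interim look at 50% of subjects. The conclusion does not depend on which slip produced 240.

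**What to change.** In "Sample size calculations" (and in the SAP if it repeats the figure):

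1. Write the formula with z for alpha/2, so that it agrees with the two-sided level in the text.
2. Replace the power statement with what 480 delivers for 65% against 76.5%: about 70% after 20% dropout and about 79% with full retention. Add that 80% power after dropout holds only for a difference of about 12.9 points.
3. State how 240 was obtained, so that the record shows whether a one-sided value was used or the dropout step was omitted.

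The figures should not be reconciled by relabelling the test as one-sided 0.05. That would double the chance of a false claim of benefit, from 2.5% to 5%.

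The cost is wording and a less favourable stated power; no extra patients are needed for the correction. If the sponsor wants a true 80% after 20% dropout, the alternative is about 614 randomised, which is a separate decision with recruitment under way since November 2023. The covariate-adjusted analysis already planned may recover some power, but the document gives no figures from which to say how much.

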### Data analysis

The missing data are processed by multiple interpolation. If the primary efficacy index is missing, the previous result is carried forward according to the intentionality analysis.If there is a valid value carried forward after randomization, the last observation is used for carry-over.

The main efficacy measure (the percentage of patients with mRS ≤ 2 ) will be compared and analyzed using the chi-squared test. The statistician will perform covariate adjusted analyses and covariate unadjusted analyses. Subgroup analyses will include sex, age, systolic blood pressure, and the baseline NIHSS score.

For dichotomous outcomes, such as the percentage of BI ≥ 90, distribution of mRS scores, proportion of early neurological deterioration, and recurrence rate of stroke, we will use the chi-squared test or Fisher’s exact test to compare the distribution of patients between the two groups.Logistic regression is utilized to estimate the 95% CI. For continuous variables, including neurological function scores, MMSE scores, PRO scale, cerebral blood flow, such as changes from baseline to treatment endpoints, Student’s t-test or Wilcoxon rank-sum test is employed to analyze the differences between the two groups.Survival data will be estimated using the Kaplan-Meier method, survival curves will be plotted, and efficacy will be evaluated using log-rank tests.

According to the safety set data, statisticians compare and analyze the differences in the incidence of adverse events, major adverse events, and liver and kidney dysfunction, as well as routine blood and urine tests between the two groups. For most safety data, Cox proportional-hazards models are used to estimate the hazard ratios between the two treatment groups.

When 50% of the subjects have completed the study, an interim analysis will be conducted. The continuation or suspension of the study is determined according to the analysis results. If the analysis results indicate that valid results cannot be obtained, the study will be terminated immediately. The study will continue if data analysis suggests that efficacy may be achieved at the end of the study.

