### Trial population

Patients from 24 hospitals in 14 provinces in China were recruited for the study (Fig. 2). The detailed inclusion and exclusion criteria are listed in Table 1.

Recruitment posters will be posted at these hospitals, so that patients can learn about the study and contact researchers. Participants were screened according to screening criteria and informed of the risks and benefits of participating in the study, as well as the collection of blood samples.If patients agree to participate in the study, they will sign an informed consent form. Recruitment began in November 2023, with initial completion expected in December 2025.If there are very serious cases of toxic side effects or insufficient recruitment, the trial will be stopped.

**Table 1 Tab1:** Inclusion and exclusion criteria

• **Inclusion criteria** • Diagnosed as having acute ischemic stroke; • Large artery atherosclerosis ischemic stroke according to the TOAST classification; • Patients with acute ischemic stroke within 48 h of onset; • Patients aged 18–80 years; • Patients with NIHSS score of 4–18 points; • An average Systolic blood pressure at least 3 times ≤ 155 mmHg before the patient’s enrollment; • Being informed about the study and signing informed consent.	• **Exclusion criteria** • Patients who have received intravenous thrombolysis or intravascular treatment; • Posterior circulation infarction; • Stroke caused by tumors; • Previous history of stroke and mRS ≥ 2 points before the onset of this stroke; • NIHSS 1a > 2 points; • Patients with a yellow and greasy tongue layer; • Patients with other diseases that limit the evaluation of neurological function or affect patient follow-up; • Patients with severe abnormal liver and kidney function with serum ALT, AST, or SCr over two times the upper limit of the reference range; • Have another serious life-threatening illness with life expectancy of less than 3 months; • Pregnant, with recent family planning, or lactating women; • Currently participating in other interventional clinical trials.

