### Primary outcome

The main efficacy measure will be the percentage of patients with the ability to engage in “relatively independent” daily living (Modified Rankin Scale ≤ 2, which is defined as relative independence) at D90.

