### Secondary outcomes

Secondary outcomes will include the following: the percentage of early neurological deterioration (defined as an increase of 2 or more points in the NIHSS score at D3 compared to baseline), the degree of neurological deficiency (measured by the change in the NIHSS scale between baseline and D10), patient self-reported outcome (measured by the change in the PRO scale between baseline and D10), change in Traditional Chinese medicine syndrome (evaluated using a stroke syndrome elements scale at baseline and D10), degree of disability (evaluated by the distribution of mRS scores at D30 and D90), proportion of patients capable of performing daily living activities (evaluated by BI scale scores at D30 and D90), mental status assessment (evaluated using MMSE scores at D90), recurrence rate of cerebrovascular events and stroke-related mortality within 90 days of onset, and incidence of important vascular events within 90 days.

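### A missing 90-day mRS is filled by carrying the previous score forward, although the plan names multiple imputation for missing data and the only earlier scores are from Day 30 or the acute phase

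*Protocol article*

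**What the plan says.** The primary outcome is the proportion of patients who are relatively independent at Day 90 ("Modified Rankin Scale ≤ 2, which is defined as relative independence").

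The Data analysis section opens with a general rule: "The missing data are processed by multiple interpolation". This is presumably multiple imputation. The next sentence treats the primary outcome separately: "If the primary efficacy index is missing, the previous result is carried forward according to the intentionality analysis". A third sentence adds a condition: "If there is a valid value carried forward after randomization, the last observation is used for carry-over".

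Appendix C lists mRS at screening, Day 1, Day 30 and Day 90, and not at Days 3, 7 or 10. The Secondary outcomes section likewise names two follow-up times for the scale: "degree of disability (evaluated by the distribution of mRS scores at D30 and D90". Patients enter within 48 hours of onset, and Table 1 requires: "Patients with NIHSS score of 4–18 points".

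On dropout, the Sample size calculations section says: "Considering a 20% dropout rate, each group should include 240 cases, bringing the total number of cases to 480".

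**The concern.** Carrying a score forward assumes that the patient would not have changed between that score and Day 90. The trial measures recovery after stroke, and the plan itself reads mRS at both Day 30 and Day 90, so no change is a poor default. Because the visits are so sparse, the gap is at least about two months (Day 30 to Day 90) and may be nearly the whole follow-up (Day 1 to Day 90). The carried value then enters the chi-squared test as if it had been observed, with no allowance for its uncertainty.

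Three things are at stake:

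- **Attenuation.** If carried scores are unrelated to treatment, they dilute a real effect and cost power.
- **Bias.** If dropout differs between arms, the carried scores create a difference where there is none, in either direction. The section on management of adverse events withdraws patients after serious adverse events, so dropout related to outcome is possible.
- **An undecided case.** The plan does not say whether Day 1 is a valid post-randomisation value. If it is not, a patient lost before Day 30 has nothing to carry. The general imputation sentence might then apply, but the text does not say so.

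**Working it through.** **Inputs from the Sample size calculations section.** Success rates 65% (control) and 76.5% (active), two-sided α 0.05, 240 per arm, 20% dropout.

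**Assumed, because the documents do not give them.** The timing of dropout; the chance q that an early carried score is 2 or below; and the ratio r of the carried Day 30 success rate to the Day 90 rate.

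**Formula.** Power = Φ[(Δ − 1.96·SE0)/SE1], where SE0 = √(2p̄(1−p̄)/n) and SE1 = √([p1(1−p1)+p2(1−p2)]/n).

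**Reference points.** A two-sided test at 80% power needs 245 per arm before any dropout allowance. The stated 240 is therefore not reproduced once 20% dropout is added (245/0.8 gives 307). That is a separate matter, and this point does not rest on it. The comparators needed here are:

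- 240 per arm, complete data: (0.115 − 1.96×0.04153)/0.04119 = 0.82, power 79%.
- 192 completers per arm (240×0.8), nothing carried: (0.115 − 1.96×0.04643)/0.04606 = 0.52, power 70%.

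**Case A: all dropout before Day 30, Day 1 score carried.** Arm rate = (1−d)·p + d·q, the same d in both arms.

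- d = 20%, q = 0: 0.8×0.65 = 52.0% and 0.8×0.765 = 61.2%. Difference 9.2 points; (0.092 − 1.96×0.04524)/0.04505 = 0.07, power 53%.
- d = 20%, q = 0.5: 62.0% and 71.2%. Difference again 9.2 points, power 57%.
- d = 10%, q = 0 to 0.5: difference 10.35 points, power 66–69%.
- d = 5%, q = 0 to 0.5: difference 10.9 points, power 72–74%.

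**Case B: all dropout after Day 30, Day 30 score carried.** Arm rate = 0.8·p + 0.2·r·p.

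- r = 0.8: 62.4% and 73.4%, difference 11.0 points, power 74%.
- r = 1: 65% and 76.5%, power 79%.

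**Mixed case.** With 5% lost early as failures and 15% lost after Day 30, power is 68–72% for r = 0.8 to 1.

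**No drug effect (65% in both arms), dropout before Day 30.** False difference = (d1 − d2)(0.65 − q), where d1 and d2 are the two arms' dropout rates.

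| Dropout | q = 0 | q = 0.2 | q = 0.4 |
|---|---|---|---|
| 20% vs 20% | 0; type I 0.05 | 0; 0.05 | 0; 0.05 |
| 20% vs 15% | 3.25 points; 0.11 | 2.25; 0.08 | 1.25; 0.06 |
| 20% vs 10% | 6.5 points; 0.30 | 4.5; 0.17 | 2.5; 0.09 |

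Heavier dropout on control produces a false benefit; heavier dropout on active produces a false harm.

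**The case against.** The strongest reply is that the damaging figures need a particular reading and a particular pattern of dropout. The plan makes carry-forward conditional on a valid value after randomisation. Appendix C takes the first Barthel and MMSE scores on Day 1, so Day 1 can fairly be read as baseline. Patients lost before Day 30 would then have nothing to carry, and imputation might apply to them. If most losses come after Day 30, power is 74–79%, above the 70% from completers alone. The 20% is a planning allowance, and nothing in this blinded, placebo-controlled design points to a 5- or 10-point imbalance. All of this stands as a limit on size. It does not rescue the rule: the ambiguity about Day 1 is itself a fault in the text, and a Day 30 score is still counted as a Day 90 observation.

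A reader might also infer three stronger points that the documents do not support:

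- **That the rule contradicts the sample size.** Inflating enrolment for dropout does not commit the analysis to excluding dropouts, so there is no contradiction.
- **That a Day 1 score is nearly always a failure.** Entry goes down to NIHSS 4 and no Day 1 mRS distribution is given, so q must be shown as a range.
- **That patients who die would carry a score from before death.** Nothing says a death counts as a missing mRS, and the Secondary outcomes section includes stroke-related mortality to 90 days.

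**Conclusion.** The point holds. For its primary outcome the plan states a single-value carry-forward rule that sits unreconciled beside a general imputation rule. Given the visit chart, the carried value is either a Day 30 score or, on one reading, an acute-phase score.

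The size is uncertain and should be quoted as a range. Under equal 20% dropout it runs from severe (power 53–57%, all losses before Day 30) to little or none (74–79%, all losses after Day 30), and the fair comparators are 79% with full data and 70% with completers. The 53% figure, and the false differences of 3.25 and 6.5 points, are worst cases: every dropout is early and every carried score is a failure. With equal dropout and no drug effect the false-positive rate is not inflated. Inflation needs unequal dropout, which the documents neither predict nor rule out. The case for changing the rule is that it governs the primary result and that the plan already names a better method.

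**What to change.** Reconcile the sentences in the Data analysis section so that one rule covers the primary outcome:

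- Make multiple imputation the primary method for a missing Day 90 mRS, run by arm, using data already scheduled: age, baseline NIHSS, NIHSS at Days 3, 7 and 10, and mRS and Barthel index at Day 30. This also settles the case of patients lost before Day 30.
- Analyse all randomised patients.
- State that known deaths count as mRS 6 and are neither imputed nor carried forward. This is a clarification worth adding; the article's silence on it is not an error.
- Keep last observation carried forward only as a labelled sensitivity analysis, ideally beside a delta-adjusted (tipping-point) one. If it is kept, say whether a Day 1 score may be carried.

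The cost is wording in the analysis plan and a little programming. No new data or visits are needed. The change should be fixed before unblinding.

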### Randomization and blinding method

Four hundred and eighty eligible patients with acute ischemic stroke will be randomized to treatment and control groups in a 1:1 ratio using a central randomized approach by investigators within 48 h of symptom onset. Figure 3 shows the flowchart of the included subjects in this study. An independent third-party “Independent Data Committee” will be responsible for the design of randomization schemes and the management of randomization systems.The method of stratified blocked randomization will be utilized to generate a random number grouping table using the professional statistical software PROC PLAN. A random allocation scheme will then be created, with a block size set to 4. It is required that there be 2 treatment groups and 2 control groups in the scheme.

The packaging, weight, and size of the two groups of drugs should be consistent. The allocation sequence and drug coding will be generated by an independent third-party “Independent Data Committee”. The process of drug coding configuration will be recorded in writing and confirmed by the corresponding participants. The researcher of this study will enroll patients strictly based on the order of random allocation table numbers. Researchers will implement randomization by using an online randomization system. They will log into the EDC system to apply for patient randomization codes and drug codes. Afterward, they will submit the requested drug code to the medication administrator.

The researcher and research assistant responsible for enrolling patients, collecting patient clinical information, and assessing outcomes, as well as participants and care providers, are blinded during the research process. Specialized personnel from each unit will be responsible for drug preparation. Dark brown infusion bags and infusion sets will be used for drug infusion to ensure the same appearance of drugs in the two groups.The recovery of relevant infusion supplies and remaining drugs will also be the responsibility of a dedicated person. Throughout the study, the researcher responsible for drug use will record the usage of the investigational drug but will not participate in the collection of other information from the subjects or exchange drug grouping information with others.

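### The primary chi-squared test is valid but forgoes power by leaving out centre, baseline NIHSS and age, and the plan does not say whether the adjusted or the unadjusted result decides

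*Protocol article*

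**What the plan says.** In the protocol article, Data analysis, the main efficacy measure "will be compared and analyzed using the chi-squared test". The next sentence reads "The statistician will perform covariate adjusted analyses and covariate unadjusted analyses". It names no covariates, no model and no order of precedence. Age and baseline NIHSS appear in that section only as subgroup factors: "Subgroup analyses will include sex, age, systolic blood pressure, and the baseline NIHSS score".

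Study design describes "stratified blocked randomization by the study center", and Randomization and blinding method gives a scheme "with a block size set to 4". Trial population puts the number of centres at 24, so 480 / 24 = 20 patients per centre on average. Centre is not mentioned anywhere in Data analysis.

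Table 1 admits a wide range on both prognostic variables: "Patients with NIHSS score of 4–18 points" and "Patients aged 18–80 years". Both are known before treatment starts.

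Sample size calculations uses an unadjusted comparison of two proportions, 65% against 76.5%, so the sizing and the named test agree.

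**The concern.** There are two separate issues.

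**Efficiency.** The named test uses neither the stratification factor nor two baseline variables that plausibly predict mRS ≤ 2. Using them needs no extra patients, visits or data. The trial has little power to spare: the stated 240 per group does not meet the stated target once the stated dropout is taken off (see the working).

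**Ranking.** An adjusted and an unadjusted result will both exist. The text implies that the chi-squared result is primary but does not say so. If the two fall on opposite sides of 0.05, nothing in the text settles which is the trial's answer, and a choice made after seeing both would raise the false-positive rate.

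**Working it through.** **Inputs from the protocol article.** Control 65%, intervention 76.5%, two-sided 0.05, target power 0.8, 20% dropout and 240 per group (Sample size calculations); 24 centres (Trial population); blocks of 4 (Randomization and blinding method).

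**Assumed inputs, not in the documents.** NIHSS and age are represented by one normally distributed score with log-odds SD 0.5, 1.0 or 1.5, which corresponds to an AUC of 0.63, 0.74 or 0.81. Between-centre SD is 0.3 on the logit scale, with one check at 0.6.

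**1. The plan's own figure.** The article's formula is 2pq(zα + zβ)² / (p1 − p2)², with p = (0.65 + 0.765)/2 = 0.7075 and q = 0.2925:

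2 × 0.7075 × 0.2925 × (1.96 + 0.8416)² / 0.115² = 245.6, so 246 per group before dropout.

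246 / 0.8 = 307.5, so 308 per group after dropout. The stated 240 is not reproduced. That is a separate point, but it fixes the power from which this one starts.

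**2. Power of the planned test.** Power = Φ{[0.115 − 1.96 √(2pq/n)] / √[(p1q1 + p2q2)/n]}.

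- n = 192 (240 × 0.8): (0.115 − 1.96 × 0.04643) / 0.04606 = 0.521, power 69.9%.
- n = 240: (0.115 − 1.96 × 0.04153) / 0.04119 = 0.816, power 79.3%.

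**3. Simulated power.** There were 6,000 trials per setting, with blocks of 4 within 24 centres, centre SD 0.3 and marginal rates held at 65% and 76.5%. The adjusted model was a logistic regression on treatment and the score, without centre. Centre was examined separately with a Cochran-Mantel-Haenszel (CMH) test.

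| Per arm | AUC | Chi-squared | Adjusted | CMH by centre | Gain, adjusted | Chi-squared and adjusted disagree at 0.05 |
|---|---|---|---|---|---|---|
| 192 | 0.63 | 70.1% | 72.1% | 70.6% | 2.0 | 6.6% |
| 192 | 0.74 | 70.4% | 76.7% | 70.7% | 6.3 | 11.4% |
| 192 | 0.81 | 69.7% | 82.2% | 69.8% | 12.5 | 16.8% |
| 240 | 0.63 | 79.4% | 80.8% | 79.8% | 1.4 | 4.6% |
| 240 | 0.74 | 79.7% | 86.1% | 79.9% | 6.4 | 9.3% |
| 240 | 0.81 | 79.7% | 90.1% | 79.9% | 10.4 | 12.8% |

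With centre SD 0.6, score SD 1.0 and 192 per arm, the chi-squared test has 70.4% power, CMH 72.1% and the adjusted model 76.0%. A second simulation (1,500 trials per setting, 192 per arm) gave adjusted gains of 1.5, 5.1 and 7.8 points at AUC 0.63, 0.71 and 0.75.

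**4. Simulated type I error, 192 per arm.**

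| AUC | Chi-squared | Adjusted | CMH | Either chi-squared or adjusted significant |
|---|---|---|---|---|
| 0.63 | 5.5% | 5.9% | 5.8% | 6.9% |
| 0.74 | 5.2% | 5.0% | 5.5% | 7.0% |
| 0.81 | 5.1% | 5.0% | 5.2% | 7.5% |

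The Monte Carlo standard error at 5% is √(0.05 × 0.95 / 6000) = 0.28 points. The first row runs high for all three tests, which share the same simulated data sets. Another run of that setting gave 4.7%, 5.3% and 5.0%. Each single test is therefore close to nominal. The last column shows the cost of leaving the choice open.

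**The case against.** The case for leaving the text alone is substantial, and much of it stands.

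- **A primary test is named.** The chi-squared test is attached to the main efficacy measure, and the natural reading is that adjustment is additional. This stands as the likely intent, but one clause would make it explicit.
- **Covariates are not shown to be ignored.** A reader might infer that the plan disregards NIHSS, age and centre altogether. The text does not support that: adjusted analyses are promised, and these variables may be among the covariates. The covariate list and model are commonly left to the statistical analysis plan, which is not shown, so their absence is no finding. The point concerns the stated choice of primary test and the missing ranking.
- **The test is valid and consistent with the sizing.** A reader might infer that ignoring the stratification makes the chi-squared test wrong, or that the trial loses power against its own plan. Neither holds. Type I error stays near 5%, and the trial was sized for an unadjusted comparison. The power is forgone, not lost against the plan.
- **Centre matters little.** The gain from centre alone is 0.1 to 0.5 points, or 1.7 points with the larger assumed centre effect. The efficiency argument rests on NIHSS and age.
- **192 per arm may be too pessimistic.** Data analysis carries a previous result forward when the primary outcome is missing, so the analysed number could be close to 240 per arm, where the chi-squared test has 79.3% power before any dilution from imputation. The gain from adjustment is similar there (1.4 to 10.4 points).

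**Conclusion.** The point holds as an inexpensive improvement and a clarification, not as an error in the test. The direction of the gain is firm. Its size, about 2 to 12 points at 192 per arm, depends on assumed prognostic strengths (AUC about 0.63 to 0.81) that the documents do not supply.

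The ranking matters more than its brevity in the text suggests. Under the planned effect, the two analyses disagree on significance in about 7% to 17% of trials at 192 per arm. If either could be called primary, the false-positive rate is about 7% to 7.5%. That figure describes what an open choice would cost. The documents do not say that anyone intends to choose.

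A reader might also infer that adjustment makes up for the sample-size shortfall. It does not do so reliably: at 192 per arm it reaches 80% only under the strongest assumed covariates.

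**What to change.** Before the first level of unblinding, and before anyone choosing the model has seen interim results by group:

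1. Define the primary analysis as a logistic regression of mRS ≤ 2 at 90 days on treatment, baseline NIHSS (continuous), age (continuous) and centre. With about 20 patients per centre, use a random intercept or pool small centres by a rule fixed in advance.
2. Report the adjusted odds ratio together with the standardised risk difference, each with a 95% confidence interval.
3. Label the chi-squared test as supportive.

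If the sponsor prefers to keep the chi-squared test as primary, one sentence is enough: it alone decides the trial, and all adjusted results are supportive.

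The cost is wording and a little more analysis work, with no added patients, visits or data. The odds ratio becomes conditional on the covariates, and the standardised risk difference beside it keeps the result readable on the scale used for sizing. The sample-size statement must still be corrected in its own right.
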